## Methods

### Study Design

RCTs, a top-level research methodology in the area of evidence-based medicine [47], have played a significant role in evaluating the effects of lifestyle changes on metabolic syndrome [48-50]. This protocol is a longitudinal pilot study that uses a 3-arm parallel-group RCT to examine the interventional efficacy of an at-home immersive VR exergame on several clinical risk factors of metabolic syndrome among office workers. On the basis of prior research on exercise and physical activity interventions [48,51], a 12-week duration was selected for this trial, as it is a commonly used period for evaluating the efficacy of interventions targeting metabolic syndrome. Several clinical risk factors for metabolic syndrome, as well as active and sedentary behavior, will be monitored in three stages during this 12-week trial. Stage 1 will be at the start of the trial, Stage 2 at week 6, and Stage 3 at the end of the trial. The therapeutic effects of the at-home immersive VR exergame intervention for metabolic syndrome will be evaluated by comparing these risk factors among three groups: the VR exergame intervention group, the regular physical activity control group, and the nonexercise control group. The study follows two checklists: the CONSORT-EHEALTH (Consolidated Standards of Reporting Trials Statement for Randomized Controlled Trials of Electronic and Mobile Health Applications and Online TeleHealth) [52] and the SPIRIT (Standard Protocol Items: Recommendations for Interventional Trials; Multimedia Appendices 1 and 2) [53,54].

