### Study Procedure

Each group in this study will consist of 40 randomly allocated participants (using a simple computer-generated random number sequence managed by JZ), and the trial will be conducted in a single-blinded structure. In this three-arm study, participants will receive the VR exergame intervention, regular physical activity, or no exercise at all. The participants will inherently be aware of their assigned activity. However, they will be blinded to the specific study hypotheses and the detailed objectives regarding comparing the 3 groups. To reduce perceived differences, participants in both control groups will receive VR exergame devices after completing the trial, but no data will be collected from this phase. Additionally, outcome assessors and data analysts will remain blinded to group assignments to prevent bias in data collection and analysis. This single-blind design helps reduce bias in the interpretation of the study results, even though participants are aware of their assigned activity.

The comprehensive framework for this protocol consists of 3 stages over 12 weeks and the allocation of items for each stage is shown in Table 2. In stage 1, when participants arrive at the data collection center, experiment coordinators will distribute and explain the manual booklet to all participants, which includes a description of the procedures, requirements, and address for inquiries. After participants have confirmed the contents and requirements of the manual, the experiment coordinators and clinic nurses will collect demographics, clinical risk factors, and GPAQ from all participants as the baseline data. A Meta Quest 2 set of equipment (entire trial), GPAQ questionnaire (0 to 6 weeks), and a recording sheet of exergaming time (0 to 6 weeks) will be additionally assigned to the VR exergame intervention group. In stage 2, the GPAQ questionnaire (7 to 12 weeks) will be assigned to all 3 groups and a recording sheet of exergaming time (7 to 12 weeks) will be additionally assigned to the VR exergame intervention group. In stage 3, only the Meta Quest 2 set of equipment will be assigned to both control groups. The necessary items for each stage will be passed to participants when they arrive at the data collection center.

**Table 2 table2:** Timeline and allocation of items.

	Stage 1^a^	Stage 2^b^	Stage 3^c^

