VR^d^ exergame intervention group	Manual booklet Demographic questionnaire GPAQ^e^ Meta Quest 2 set Recording sheet of exergaming time	GPAQ Recording sheet of exergaming time	—^f^
Regular physical activity control group	Manual booklet Demographic questionnaire GPAQ	GPAQ	Meta Quest 2 set
Nonexercise control group	Manual booklet Demographic questionnaire GPAQ	GPAQ	Meta Quest 2 set

^a^Start of the trial.

^b^Week 6 of the trial.

^c^End of the trial.

^d^VR: virtual reality.

^e^GPAQ: Global Physical Activity Questionnaire.

^f^Not applicable.

All participants will be asked to visit the data collection center in three stages for data collection and experimental material allocation. The self-reported GPAQ questionnaire will be completed by all participants at home, as it is a convenient at-home format for exploring impacts on active and sedentary behavior. The VR exergame intervention group will record the frequency and duration of their exergaming sessions, the regular physical activity control group will track their daily exercise routines, and the nonexercise control group will report any physical activities they perform beyond their baseline. Participants will be asked to bring all self-report sheets to the data collection center at stages 2 and 3. Coordinators will collect and summarize all the completed questionnaires and recording sheets for data processing. Major clinical risk factors are objectively measured from participants’ metabolic syndrome biomarkers, which are operated by professional nurses at the data collection center (cooperative clinic). Since there is a fasting biomarker for testing metabolic syndrome, all participants are required not to consume any food or drink 12 hours before blood sample collection in the morning. After the major clinical risk factor data from all the participants for the entire trial are collected, the experiment coordinators will visit and obtain the data from the data collection center.

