## Discussion

### Principal Findings

Our findings will reveal whether the clinical risk factors for metabolic syndrome within the intervention group significantly improved after a 12-week exergaming intervention compared with those in the two control groups. The increase in the time engaged in physical activity (all types of light, moderate, and vigorous intensity) and the decrease in the time spent in sedentary behavior will also be evaluated.

The phenomenon of physical inactivity among employed adults has been occurring increasingly worldwide because of the development of society and technology in recent decades [16,17]. Consequently, the population of employed adults at risk for metabolic syndrome is growing across the globe [14,15]. Several primary factors, such as a lack of motivation, weather restrictions, and busy schedules for work, social lives, and family, have been reported as key barriers to physical activity [34]. Notably, at-home immersive VR exergames can provide several advantages to address these barriers to physical inactivity for employed adults. However, to our knowledge, few studies have explored the health effects of immersive exergames. This study is the first RCT and aims to examine the effectiveness of at-home immersive VR exergame interventions for improving metabolic syndrome. Our hypotheses were based on several advantages of at-home immersive VR exergames. The first benefit to exergames is engagement and enjoyment, as various types of motivational affordances (eg, points, leaderboard, and badges) were found within the gaming process along with several positive psychological effects (eg, joyfulness) [76]. The second advantage is the convenience of at-home exercise, which can mitigate weather restrictions and fit into a flexible schedule. In addition, exergames also have positive impacts on both physical health and cognition [77], which may offer pathways to improve rehabilitation and wellness [41]. Although these positive results have been reported, there is also some evidence that these positive impacts from exergames may be temporary [78].

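### The GPAQ procedure does not give comparable activity and sedentary values at start, week 6 and end of trial: baseline is taken at the centre, follow-up on take-home forms labelled for six-week periods

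*Protocol article*

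**What the plan says.** Study Design fixes the assessment times as points: "Stage 1 will be at the start of the trial, Stage 2 at week 6, and Stage 3 at the end of the trial". Table 1 ticks exercise time and sedentary time at all three.

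Study Procedure then describes how the GPAQ is obtained:

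- **Baseline.** At the stage 1 visit, "the experiment coordinators and clinic nurses will collect demographics, clinical risk factors, and GPAQ from all participants as the baseline data".
- **First follow-up form.** Also at stage 1, a "GPAQ questionnaire (0 to 6 weeks), and a recording sheet of exergaming time (0 to 6 weeks) will be additionally assigned to the VR" exergame group.
- **Second follow-up form.** "In stage 2, the GPAQ questionnaire (7 to 12 weeks) will be assigned to all 3 groups".
- **Stage 3.** No GPAQ is handed out: "In stage 3, only the Meta Quest 2 set of equipment will be assigned to both control groups". Table 2 agrees, showing the GPAQ at stages 1 and 2 only.
- **Completion.** "The self-reported GPAQ questionnaire will be completed by all participants at home".
- **Return.** "Participants will be asked to bring all self-report sheets to the data collection center at stages 2 and 3".

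The Analyses section reports the result as weekly minutes by intensity, plus sedentary time.

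**The concern.** The second stated objective is the effect of the exergames on active and sedentary behaviour. The abstract adds that changes in behaviour will help to determine the effect on metabolic syndrome. That needs three values per participant that measure the same thing, in the same way, at the three stages.

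As described, the baseline value is taken by staff at the centre before the intervention starts. The later values come from forms that the participant holds for up to six weeks, completes alone and returns at the next visit. The form carries a six-week label, but the result is reported per week. A change from baseline then contains a change of reference period and, if the baseline description is taken at its word, a change of setting. The pilot is meant to supply effect estimates for a larger trial, so an unclear behavioural measure would be carried forward.

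**Working it through.** The article gives no figure for this point to reproduce. The check is a comparison of the text, followed by one illustration under a stated assumption.

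**Step 1. Source of each value required by Table 1**

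| Value | Where completed | Form | Period on form |
|---|---|---|---|
| Stage 1 | Centre (baseline description); home (general sentence) | Collected at the stage 1 visit | None stated; precedes the intervention |
| Stage 2, VR arm | Home | Issued at stage 1 | Weeks 0 to 6 |
| Stage 2, control arms | Not stated | No such form in the text | Not stated |
| Stage 3, all arms | Home | Issued at stage 2 | Weeks 7 to 12 |

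The stage 3 value must come from the form issued at week 6, because none is issued at stage 3.

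**Step 2. Count the forms.** Each participant needs 3 values. The text provides 1 + 1 + 1 = 3 forms in the VR arm and 1 + 1 = 2 in each control arm. Table 2 shows 2 GPAQ entries (stages 1 and 2) in every arm. The stage 1 entry in Table 2 may stand for both a baseline and a take-home form in all arms, but the text assigns the take-home form additionally to the VR arm only. The two need reconciling.

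**Step 3. What a follow-up value describes.** The return visit gives a latest date: week 6 for the first form and week 12 for the second. The article gives no earliest date and no recall period beyond the labels. Three readings remain open: the time of completion, a typical week, or an average over the six weeks.

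**Step 4. Why the reading matters (illustration).** Assume that behaviour changes linearly from week 0 to week 12. This is an assumption, not a figure from the article.

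- Average over the first window: midpoint week 3, which shows 3/6 = 50% of the week 6 change.
- Average over the second window: midpoint week 9, which shows 9/12 = 75% of the week 12 change.
- Time of completion, first form: any point from week 0 to week 6, so 0/6 to 6/6 = 0% to 100% of the week 6 change.
- Time of completion, second form: any point from week 6 to week 12, so 6/12 to 12/12 = 50% to 100% of the week 12 change.

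Under a different assumption, that behaviour shifts at once and then stays level, every reading gives 100% and nothing is distorted. If behaviour rises and then falls, an early or averaged value exceeds the week 12 value. The sign and size therefore depend on a time course that the article does not give.

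**The case against.** Several points on the other side stand, in whole or in part.

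- **The forms do have a link to the stages.** Their labels end at weeks 6 and 12 and they are returned at those visits. It would be wrong to call them unconnected to the stages. What is open is the completion day and the recall period.
- **The missing completion day rests partly on silence.** The article is condensed, and the manual booklet given to all participants may name a day. It would not alter the stated six-week labels, the early issue of forms or the difference from baseline.
- **A period-based form has some rationale.** The Analyses section also summarises risk factor change over the first and last six weeks. Baseline, however, has no matching period, and Table 1 presents all three values as one series.
- **Adherence does not depend on the GPAQ.** It is taken from daily self-report logs, which also supply the covariate and the sensitivity analyses.
- **The weakness of self-report is disclosed.** The limitations say that unsupervised recording and self-reported GPAQ items may be inexact. They do not mention timing, setting or reference period.

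A reader might infer more: that late activity in the VR arm will be overstated, since the Discussion says that "there is also some evidence that these positive impacts from exergames may be temporary". For example, suppose play fell linearly from 150 minutes a week at week 6 to between 100 and 50 at week 12. A form describing week 7 would give 150 − 50/6 = 142 or 150 − 100/6 = 133 minutes, which is 42 or 83 above the week 12 value. The documents do not support this as a finding. The decline is assumed. The Discussion sentence follows one on physical health and cognition, and gives neither a play time nor a time scale. A form completed at week 7 also cannot summarise weeks 7 to 12. If it did average that window, the same assumption would give (150 + 100)/2 = 125 or (150 + 50)/2 = 100, a gap of 25 or 50. Nothing shows that early completion is likely.

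**Conclusion.** The point holds in a limited form. The stated procedure does not deliver GPAQ values that are comparable across the three stages in Table 1. Follow-up values are bounded only by a latest return date, their reference period is unclear and differs from that of baseline, and the setting differs too if baseline is completed at the centre. The article contradicts itself on that last matter, because the sentence on home completion makes no exception for baseline. It also leaves the source of the control arms' stage 2 value unstated.

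Neither the size nor the direction of any resulting bias can be derived. The percentages above show only how far the reading of the form matters under an assumed linear change. The consequence is confined to the secondary aim on active and sedentary behaviour. The primary clinical risk factors are measured by nurses at the visits and are not affected. The change should be made because it is cheap and the behavioural aim depends on it, but the problem does not threaten the primary comparison.

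**What to change.** In Study Procedure and Table 2, have all three arms complete the GPAQ at the data collection centre at each of the three visits already scheduled. Use the same mode of completion and the same recent reference period each time, and complete it before new materials are handed out. Remove the take-home GPAQ forms with six-week labels, keep only the activity logs for home use, and show the GPAQ at stages 1, 2 and 3 for every arm in Table 2. Delete or reword the sentence on home completion.

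This aligns the GPAQ with the clinic measurements, settles where baseline is completed and gives the control arms a stage 2 value. The cost is a few minutes per visit, the rewording, and the loss of the convenience for which home completion was chosen. No extra visit is needed.

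If home completion is kept, the minimum is to state one completion day and one reference period for each stage, identical in all arms and matched at baseline, and to say which arms receive the first follow-up form. That would leave any difference in setting from baseline unless baseline is completed the same way.

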### Participant Recruitment

For this exploratory study, a convenience sampling method will be used to recruit 120 office workers from six office-oriented information technology companies in Guangzhou City, Guangdong Province, located in Southern China. This group represents a high proportion of physically inactive individuals [55,56] and is at greater risk of developing metabolic syndrome [56-58]. Recruitment emails will be sent to participants via the Tencent Enterprise Mailbox [59], a platform that allows companies to create email accounts with their corporate domain. This platform serves as a communication and office tool to support enterprises in providing unified notifications to office workers and to support office workers in providing timely and efficient feedback. The inclusion criteria for participants are office workers who are 16-60 years old (based on the standard age of the Labor Law of the People’s Republic of China), capable of standing and exercising, and have no history of heart disease, cancer, or dementia. Additionally, participants should be interested in playing with the exergames and willing to adhere to a 12-week intervention exergame treatment because of the nature of the trial.

This research aims to examine the effects of at-home immersive VR exergames on the clinical risk factors for metabolic syndrome. Hence, individuals who are already engaged in more than 150 minutes per week of moderate to vigorous intensity physical activity will be excluded [60]. Additionally, pharmacological treatments, such as metabolic syndrome–related medicines (insulin sensitizers and biguanides, orlistat, sibutramine, etc), some surgeries (bariatric surgery), and traditional Chinese medicine (herbal medicine of ginseng, berberine, bitter melon, etc), are the other exclusion criteria because of their potential to influence cardiometabolic outcomes [61,62].

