### Intervention and Control Groups

Following RCT guidelines [63,64], participants will be randomized into three equal groups: (1) the at-home immersive VR exergame intervention group, (2) the regular physical activity control group, and (3) the nonexercise control group. Including both the regular physical activity and nonexercise control groups will help determine whether VR exergame intervention offers unique benefits beyond those achieved through traditional exercise or no intervention. This design allows us to isolate the specific effects of immersive VR exergames. The at-home immersive VR exergame intervention includes a 12-week trial of exercise using Meta Quest 2, as shown in Figure 1. The Meta Quest 2 device is a valid tool that has been used in previous studies to support physical activity [65-68]. A VR headset and 2 handheld controllers are contained in the Meta Quest 2 set. Several active aerobic game apps will be installed on headset devices. These apps include the following [69]: Beat Saber (exercise: full-body, aerobic), Synth Riders (exercise: dance, aerobic), OhShape (exercise: dance, aerobic), Ragnarock (exercise: arms, shoulders, aerobic), Dance Central (exercise: dance, aerobic), Until You Fall (exercise: back, shoulders, arms, aerobic), In Death: Unchained (exercise: arms and shoulders, endurance/aerobic), and Space Pirate Trainer (exercise: full-body, aerobic). In these immersive games, the users can present their body movements in the game world from a first-person perspective. Moreover, they are all designed to motivate users to participate in physical movements with various categories of motivational affordances. For example, Beat Saber is a rhythm game in which users need to move their bodies to slice blocks at an exact angle. Physical activities such as arm waving, moving, and squatting with an accelerating speed are motivated in the game with affordances of rank, point, and record. The participants in the VR exergame intervention group will be instructed to play one or more of these exergames for at least 150 minutes per week, which is in line with the World Health Organization’s physical activity guidelines [60]. They will be requested to record the frequency and duration of their exergaming sessions. Participants in the regular physical activity control group will engage in a physical activity routine similar in duration and intensity to the VR exergame intervention. Participants in the nonexercise control group will not receive any specific exercise instructions. All groups will be advised to maintain regular eating and working habits without making significant changes throughout the 12-week trial. After completing the trial, participants in both control groups will be offered the same procedures as the intervention group, but their data will not be collected.

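### Exercise before the blood draw is neither standardised nor analysed, so contrasts with the nonexercise arm may mix a short-term effect with the 12-week effect

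*Protocol article*

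**What the plan says.** All references are to the protocol article.

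- **Sampling condition (Study Procedure).** The only stated condition is fasting: "all participants are required not to consume any food or drink 12 hours before blood sample collection in the morning". The text ties it to the fasting biomarker. No section restricts or times exercise before a visit.
- **Exercise by arm (Intervention and Control Groups).** The VR arm is told to "play one or more of these exergames for at least 150 minutes per week". The number of sessions and their days are left open. The regular physical activity arm "will engage in a physical activity routine similar in duration and intensity to the VR exergame intervention". For the third arm: "Participants in the nonexercise control group will not receive any specific exercise instructions".
- **Timing (Study Design).** "Stage 1 will be at the start of the trial, Stage 2 at week 6, and Stage 3 at the end of the trial". Stage 1 therefore precedes any assigned exercise. Stages 2 and 3 fall during or at the end of the exercise period.
- **Analysis (Analyses).** The primary outcome is the change in eight clinical risk factors, compared across arms and stages in a linear mixed model with a group-by-time term. Adherence from daily self-report logs enters as a covariate. Time since the last session does not appear.

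**The concern.** Fasting controls a short-term influence that should be much alike across arms, since all groups are told to keep their usual eating habits. Recent exercise is a short-term influence that differs by arm by design, and it is left free. It also differs by stage, because assigned exercise starts only after the baseline draw. If a session shifts a measure for a day or so, that shift is absent at stage 1 and possible at stages 2 and 3 in the two exercising arms. It then does not cancel in the change from baseline or in the group-by-time term. The adherence covariate does not separate it, because it describes how much was done and not how recently.

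The article treats the 12-week contrast as the therapeutic effect, and wants effect sizes from this pilot to plan a fully powered trial. A systematic component in the estimate does not shrink with sample size and would carry into that calculation.

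**Working it through.** The article gives no power calculation, SD or effect size, so there is no figure of its own to reproduce on this point.

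**Inputs from the article:** 40 participants per arm; at least 150 minutes a week in the VR arm and a similar amount in the regular activity arm; a morning draw after 12 hours without food or drink; stages at start, week 6 and end.

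**Assumptions (not in the article):** k sessions a week on random days; an acute effect of *a* SD lasting one day; a share p0 of the nonexercise arm active the day before the draw.

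**Step 1: share of exercisers with a session the day before the draw.** This is 1 − C(6,k)/C(7,k) = k/7.
- 2 sessions of 75 minutes: 2/7 = 29%
- 3 sessions of 50 minutes: 3/7 = 43%
- 5 sessions of 30 minutes: 5/7 = 71%

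**Step 2: expected bias in a contrast with the nonexercise arm.** Bias = a × (k/7 − p0).

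| a (SD) | k | p0 = 0 | p0 = 2/7 |
|---|---|---|---|
| 0.1 | 3 | 0.043 | 0.014 |
| 0.1 | 5 | 0.071 | 0.043 |
| 0.3 | 3 | 0.129 | 0.043 |
| 0.3 | 5 | 0.214 | 0.129 |

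With p0 = 0 the range is 0.04 to 0.21 SD. With p0 = 2/7 it is 0.01 to 0.13 SD.

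**Step 3: scale.** The standard error of a 40-versus-40 difference in means, in SD units and without dropout or covariate adjustment, is √(2/40) = 0.224 SD. The top of the range is 0.214/0.224 = 0.96 standard errors; the bottom is 0.014/0.224 = 0.06.

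**Step 4: VR versus regular activity.** If both arms keep similar schedules, the shares in Step 1 are equal and the expected bias is a × (k/7 − k/7) = 0.

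**Step 5: what a bias of 0.1 SD would do to the next trial (illustration).** At two-sided 5% and 80% power, n per arm is 2 × (1.96 + 0.84)²/d², about 15.7/d². An observed 0.5 SD gives 15.7/0.25, about 63 per arm. If the sustained effect were 0.4 SD, the need would be 15.7/0.16, about 98 per arm.

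**The case against.** **A journal article condenses.** Participants receive a manual booklet describing procedures and requirements, and a pre-visit exercise rule may sit there. That is possible and limits the weight of the point. But the article itself states the sampling condition for all participants and names food and drink only. Followed as written, exercise is left free.

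**The stronger reading.** A reader might infer that the exercising arms *are* sampled soon after a session and the controls are not. The documents do not support this. No section gives session days or the gap between the last session and a visit. One of the two control arms also exercises, at similar duration and intensity. The nonexercise arm is not inactive by rule: at entry only "individuals who are already engaged in more than 150 minutes per week of moderate to vigorous intensity physical activity will be excluded", and during the trial "the nonexercise control group will report any physical activities they perform beyond their baseline". Nor is the whole 12-week effect in question, since BMI and waist are hardly affected.

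**The harm is assumed.** Nothing in the article says that one session shifts any outcome, in which direction or for how long. This stands: the figures above show a range and do not estimate a bias.

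**The logs may already hold the information.** Analyses speaks of daily logs for all participants, from which the last active day might be recovered. However, Study Procedure describes the VR record as frequency and duration, and Table 2 issues a recording sheet to that arm only. Recovery in the same way across arms is therefore not assured.

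**Measuring people on their usual programme is a legitimate pragmatic target.** It is, but the article reads the result as a 12-week therapeutic effect and does not say that a short-term component belongs to it.

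**Conclusion.** The point holds in a limited form. Pre-visit exercise is neither standardised nor represented in the analysis, it differs by arm and by stage, and any last-session effect would not cancel in the planned comparison. The contrasts at risk are VR versus nonexercise and regular activity versus nonexercise, on measures assumed to respond quickly.

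The size depends wholly on assumed session counts, an assumed acute effect and assumed activity in the nonexercise arm. Under those assumptions it runs from negligible to just under one standard error. Fewer sessions than assumed would lower it; a larger acute effect would raise it. This does not invalidate the trial. It is worth correcting because the step is cheap and cannot be fully recovered once the samples are drawn.

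**What to change.** 1. In Study Procedure, add to the fasting sentence one pre-visit activity condition that applies to all three arms and all three stages. The clinical team sets the interval; the weekly exercise time stays as planned.
2. Record the date and time of the last exercise session at each visit, in the same way in every arm.
3. Report time since the last session by arm and stage as a descriptive, supportive check. Do not exclude recently exercised participants from the randomised comparison: that would select on behaviour after randomisation, and unequally by arm.

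Cost: one sentence in the article and the manual booklet, and one field on the visit form. Downside: a participant may have to move one session in the weeks of the stage 2 and stage 3 visits.
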